#### fNIRS system and data analysis of upper limb flexors

In this study, an OctaMon M system (Artinis, LLC, New York, NY, USA) was used to continuously measure and record changes in the concentration of HbO and HbR in the upper limb flexors during the grasp task. The system consisted of two receivers and eight transmitter probes, forming a total of eight effective channels (CHs) as shown in Figure 5. The distance between the transmitter and receiver probes was 35 mm for the OctaMon M system, and the inter-optode distance was less than 3 mm. The absorption of near-infrared light at two different wavelengths (760.0 nm and 850.0 nm) was measured, and a sampling rate of 10 Hz was used during the measurements. The channel widths were adaptable and ranged from 25 mm to 40 mm. With a 2 × 4 channel configuration, changes in oxyhemoglobin, deoxyhemoglobin, and total hemoglobin values could be regionally monitored.

**FIGURE 5 F5:**
[figure not shown]
The arrangement of fNIRS channels for upper-limb flexors.

During the experiments, the OctaMon M system was placed on the flexors of the elbow and wrist to record the parameters of interest. When locating the muscle holder 1 on the flexors of the forearm, the receiver 1 was positioned at the upper one-third distance from the external epicondyle of the humerus to the styloid process of the ulna. When locating the muscle holder 2 on the elbow flexors, the receiver 2 was positioned at the lower one-third distance from the medial epicondyle of the humerus to the acromion. The arrangement of fNIRS channels for the upper limb flexors is shown in Figure 5.

For data analysis, dedicated software called OxySoft from Elst, The Netherlands, was used to analyze the system data. The fNIRS signal was transferred directly to a PC computer using a Bluetooth device. The collected data were exported to a text file and subsequently analyzed using MATLAB software.

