### Outcomes

#### Primary outcomes

In this study, two different applications of functional near-infrared spectroscopy (fNIRS) were employed: fNIRS of the cerebral cortex and fNIRS of the upper-limb flexors.

For fNIRS of the cerebral cortex, a Huichuang portable 35-channel fNIRS system was utilized to measure blood oxygen parameters, including HbO, HbR, and HbT. The system used the continuous wavelet transform method to calculate the wavelet amplitude (WA) of signals ranging from 0.01 to 0.08 Hz in each cortical region (Huo et al., 2019a). The phase information was extracted from the signals. The inter-hemispheric lateral degeneration index was then calculated based on WA to evaluate the degree of brain activation transfer from the affected side to the healthy side. Additionally, the extracted phase information was used for effect connection analysis based on dynamic Bayesian inference to assess the strength of the interaction between the cerebral cortex regions (Huo et al., 2019a).

For fNIRS of the upper-limb flexors, a portable muscle oxygen detector called OctaMon from Artinis Medical Systems B. V. was employed. This system utilized an 8-channel near-infrared spectroscopy setup to measure blood oxygen parameters (HbO, HbR, HbT) in the flexor muscles of the upper limb. A distribution map was created based on the measured parameters. The spatial-temporal parameters of blood oxygen were analyzed to evaluate muscle activities.

Overall, both fNIRS applications aimed to investigate blood oxygen parameters in different regions of interest (cerebral cortex and upper-limb flexors) and analyze their characteristics to understand brain activation transfer, cerebral cortex interactions, and muscle activities in the context of the study.

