#### Secondary outcomes

The upper extremity section of the Fugl–Meyer assessment (FMA-UE): The FMA-UE has frequently been used to measure UE motor impairment (Prochazka and Kowalczewski, 2015; Qian et al., 2017) and has been reported to yield good intra-rater and inter-rater reliability and construct validity (Page et al., 2012). It is widely used to evaluate motor impairment in the upper extremity and has a Chinese version that is frequently employed in research (Wu et al., 2009).

Action Research Arm Test (ARAT): The ARAT was developed as a performance test to assess upper extremity function and dexterity after stroke (Lyle, 1981). A Chinese version of the ARAT (C-ARAT) has been translated and has been proved to have good validity, reliability (inter-rater reliability = 0.998, intra-rater reliability = 0.987), responsiveness, and predictive ability (Zhao et al., 2019c; Zhao et al., 2019a; Zhao et al., 2019b). The ARAT follows a hierarchical order, where the difficulty of items increases progressively.

MyotonPRO: Muscle tone of biceps and flexor carpi radialis of both upper limbs is evaluated using a portable MyotonPRO instrument. MyotonPRO demonstrated acceptable relative and absolute reliability in a ward setting for patients with acute stroke (Lo et al., 2017b).

Modified Ashworth scale (MAS): The MAS is an assessment tool commonly used to measure spasticity in individuals with stroke. The scale comprises six levels of spasticity severity, including grade 0, 1, 1+, 2, 3, and 4, which is in sequence scored 0, 1, 1.5, 2, 3, and 4 points in this study. This study assessed the flexors of elbow, wrist and fingers. MAS has also been shown to have excellent inter-rater reliability (ICC = 0.686-0.781) and intra-rater reliability (ICC = 0.644-0.748) in assessing spasticity in patients (Meseguer-Henarejos et al., 2018).

Modified Barthel Index (MBI): The MBI is a tool that is commonly used to assess the self-care ability of daily living, which reflects functional capacity, particularly in patients following stroke (Perez et al., 2018). In assessing patients following stroke, the MBI has shown excellent reliability (ICC = 0.88) (Yang et al., 2021).

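### The written landmark for the forearm optode does not fit its stated target, the forearm flexors, and followed literally would tend to place it over the extensors

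*Protocol article*

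**What the plan says.** All placement text is in the Methods section of the protocol article headed *fNIRS system and data analysis of upper limb flexors*. The general statement is that "the OctaMon M system was placed on the flexors of the elbow and wrist to record the parameters of interest". The sentence on the forearm begins "When locating the muscle holder 1 on the flexors of the forearm" and ends by giving the site: "the receiver 1 was positioned at the upper one-third distance from the external epicondyle of the humerus to the styloid process of the ulna". The sentence on the upper arm uses the other epicondyle: "the receiver 2 was positioned at the lower one-third distance from the medial epicondyle of the humerus to the acromion". The reader is then referred to Figure 5, which is not reproduced in the text at hand.

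On hardware, the same section states: "The system consisted of two receivers and eight transmitter probes, forming a total of eight effective channels". It describes the layout as 2 × 4.

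Under *Primary outcomes*, the muscle device is there "to measure blood oxygen parameters (HbO, HbR, HbT) in the flexor muscles of the upper limb", and a distribution map and spatial-temporal parameters are to be derived from its channels. The last paragraph of the *Introduction* puts flexor oxygenation and its heterogeneity in the primary objective. The *Summary* in the Discussion hypothesises altered flexor hemodynamics, including greater oxygen consumption.

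**The concern.** The target and the landmark stand in one sentence and point to different sides of the forearm. The wrist and finger flexors arise mainly from the medial epicondyle and lie on the volar side. The wrist and finger extensors arise mainly from the lateral epicondyle and lie on the dorsal side. A landmark line that starts at the lateral epicondyle is therefore an unexpected way to find the flexors.

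The forearm holder is the only muscle site near the wrist and finger flexors, the muscles most directly tied to a grasping task; the other holder covers the elbow flexors. If the forearm site were over the extensors, three things would suffer:

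- Group comparisons and changes after therapy at that site would be reported as flexor findings but would describe an antagonist or stabilising group.
- The distribution map would combine elbow flexors with forearm extensors and could not describe heterogeneity within the flexors.
- The planned correlations among parameters could pair extensor oxygenation with flexor function or tone.

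No analysis can correct a wrong recording site afterwards.

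**Working it through.** No formula or stated figure is at issue. The check compares the stated target with the stated landmark and then counts what depends on the landmark.

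**Step 1: target.** Three statements agree on flexors: the general placement sentence (elbow and wrist flexors), the opening of the holder 1 sentence (forearm flexors), and *Primary outcomes* (upper-limb flexors). The intended compartment is not in doubt.

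**Step 2: landmark.** Receiver 1 lies on a line from the external epicondyle to the ulnar styloid, at its upper third. Whether external could be a loose word for either epicondyle is answered by the next sentence, which uses the medial epicondyle for receiver 2. The text distinguishes the two sides.

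**Step 3: where that line runs.** This step rests on general anatomy, which the article does not state. The lateral epicondyle is the common extensor origin. Drawn in the usual way to the ulnar styloid, the line follows the dorsal forearm, and its upper third overlies the extensor mass. The article gives neither forearm posture nor the surface on which the line is drawn, so the step is probable, not certain.

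**Step 4: other text.** No other part of the article gives a different forearm landmark. Figure 5 may, but cannot be consulted.

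**Step 5: extent.**

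- Channels: 8 channels ÷ 2 receivers = 4 per receiver, if the 2 × 4 layout splits evenly. So 4 of 8 muscle channels, or half, depend on this landmark.
- Unaffected: the 4 elbow-flexor channels and all 35 cortical channels.
- Participants: 3 × 20 = 60 with stroke plus 20 controls = 80, each measured at least once under the same written rule. Assessment before and after the intervention is specified under *Experimental procedure* for stroke participants only. That gives 60 × 2 + 20 = 140 planned assessments if controls are measured once. This is the number governed by the sentence, not a number shown to be wrong.

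**The case against.** The strongest reply is that the compartment is already fixed. The sentence starts by saying that the holder is on the forearm flexors, so the epicondyle-to-styloid line may set only how far down the forearm the holder sits. A one-word slip, external for internal, is also plausible. Figure 5 could settle the matter. In addition, with the forearm supinated, a line from the lateral epicondyle towards the ulnar side of the wrist can be drawn obliquely across the volar surface, where it would not lie over the dorsal extensors.

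Much of this stands. A reader might infer that the primary muscle outcome was recorded from the wrong muscle group in every participant at every visit. The article does not support that: it shows what was written, not where the holder sat, and it does not specify repeat visits for controls. Nor is there a separate primary outcome for the forearm; the outcome is upper-limb flexor oxygenation, of which the forearm is one part.

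A reader might also see a conflict with the tone measurement, because *Secondary outcomes* says "Muscle tone of biceps and flexor carpi radialis of both upper limbs is evaluated using a portable MyotonPRO instrument". That inference is weak. The sentence names a muscle for a different instrument and gives no site, nothing says that the two sites should coincide, and the correlations are planned only in general terms. An argument from light penetration depth adds nothing either, because depth does not tell which compartment lies under the probe.

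The reply does not clear the text. A level-only reading has to be supplied by the reader, and a slip in the placement rule for a repeated primary measurement still needs correcting.

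**Conclusion.** The point holds for the placement as written. Followed literally, the landmark would tend to put the forearm channels, 4 of 8 on an even split, over the extensors, against the target named in the same sentence. It touches the forearm half of the muscle part of a primary outcome and nothing else.

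The conclusion rests on three assumptions: the general anatomy of the two epicondyles, the line being drawn in the usual way along the dorsal forearm, and an even division of channels between receivers. Whether any recordings came from extensors is open; if the error is only in the wording, data already collected are valid flexor data. The correction is still worth requiring, because the sentence is the operator's instruction for a primary measurement and costs almost nothing to put right.

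**What to change.** 1. Replace the holder 1 landmark with one on the flexor side, and make the text agree with the stated target and with Figure 5. One workable option is a line starting from the medial epicondyle on the volar forearm, with the forearm posture stated and the flexor belly confirmed by palpation. Other flexor-side landmarks would serve as well.
2. Verify the placement actually used so far, for example from Figure 5, site photographs or the operators' working instructions, and state it.
3. Only if recordings are found to have been made over the extensors, label them as extensor data, and neither pool them with flexor data nor report them as flexor findings. If placement was on the flexors, the data stand and only the sentence changes.

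The cost is one corrected sentence and brief operator retraining, with no new equipment or visits. The possible downside is the loss, for the flexor outcome, of forearm recordings already taken at the wrong site.

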### Interventions

In this study, two different rehabilitation interventions were used: Virtual Reality Training (VR) and Conventional Occupational Therapy (OT).

For the VR training, the Arm Guider upper limb rehabilitation training system (Shanghai ZD Medical Technology Co., Ltd, China) was used. This system is specifically designed for individuals with upper limb dysfunction and provides various modes of training, including passive, assisting, active, and resistance training. The goal of VR training is to enhance proprioception, promote brain function remodeling, and reconstruct the neural system network. It combines exercise training with immersive game scenes to improve control, coordination, strength, and joint motion of the upper limbs, as well as train memory, understanding, and spatial structure imagination. During the first training session, the range of movement was individually set up, and the training mode was selected based on the residual motor function of the affected upper extremity. Real-time visual feedback was provided through a monitor located approximately 1 meter away from the patients to assist in task-oriented training. Additionally, real-time auditory feedback was given to indicate the quality of performance. The training sessions were conducted by an experienced occupational therapist for 30 min each, with rest intervals. The VR training was administered once a day, five times a week, for a total of three consecutive weeks.

Conventional OT was also performed by the same occupational therapist who had 15 years of experience in stroke occupational treatment. The OT treatment primarily focused on traditional neuromuscular promotion techniques, including joint compression, muscle extension, upper limb and hand functional training, and activities of daily living (ADL) training. Each OT session lasted for 30 min and was conducted once a day, five times a week, for three consecutive weeks.

### Outcomes

#### Primary outcomes

In this study, two different applications of functional near-infrared spectroscopy (fNIRS) were employed: fNIRS of the cerebral cortex and fNIRS of the upper-limb flexors.

For fNIRS of the cerebral cortex, a Huichuang portable 35-channel fNIRS system was utilized to measure blood oxygen parameters, including HbO, HbR, and HbT. The system used the continuous wavelet transform method to calculate the wavelet amplitude (WA) of signals ranging from 0.01 to 0.08 Hz in each cortical region (Huo et al., 2019a). The phase information was extracted from the signals. The inter-hemispheric lateral degeneration index was then calculated based on WA to evaluate the degree of brain activation transfer from the affected side to the healthy side. Additionally, the extracted phase information was used for effect connection analysis based on dynamic Bayesian inference to assess the strength of the interaction between the cerebral cortex regions (Huo et al., 2019a).

For fNIRS of the upper-limb flexors, a portable muscle oxygen detector called OctaMon from Artinis Medical Systems B. V. was employed. This system utilized an 8-channel near-infrared spectroscopy setup to measure blood oxygen parameters (HbO, HbR, HbT) in the flexor muscles of the upper limb. A distribution map was created based on the measured parameters. The spatial-temporal parameters of blood oxygen were analyzed to evaluate muscle activities.

Overall, both fNIRS applications aimed to investigate blood oxygen parameters in different regions of interest (cerebral cortex and upper-limb flexors) and analyze their characteristics to understand brain activation transfer, cerebral cortex interactions, and muscle activities in the context of the study.

#### Secondary outcomes

The upper extremity section of the Fugl–Meyer assessment (FMA-UE): The FMA-UE has frequently been used to measure UE motor impairment (Prochazka and Kowalczewski, 2015; Qian et al., 2017) and has been reported to yield good intra-rater and inter-rater reliability and construct validity (Page et al., 2012). It is widely used to evaluate motor impairment in the upper extremity and has a Chinese version that is frequently employed in research (Wu et al., 2009).

Action Research Arm Test (ARAT): The ARAT was developed as a performance test to assess upper extremity function and dexterity after stroke (Lyle, 1981). A Chinese version of the ARAT (C-ARAT) has been translated and has been proved to have good validity, reliability (inter-rater reliability = 0.998, intra-rater reliability = 0.987), responsiveness, and predictive ability (Zhao et al., 2019c; Zhao et al., 2019a; Zhao et al., 2019b). The ARAT follows a hierarchical order, where the difficulty of items increases progressively.

MyotonPRO: Muscle tone of biceps and flexor carpi radialis of both upper limbs is evaluated using a portable MyotonPRO instrument. MyotonPRO demonstrated acceptable relative and absolute reliability in a ward setting for patients with acute stroke (Lo et al., 2017b).

Modified Ashworth scale (MAS): The MAS is an assessment tool commonly used to measure spasticity in individuals with stroke. The scale comprises six levels of spasticity severity, including grade 0, 1, 1+, 2, 3, and 4, which is in sequence scored 0, 1, 1.5, 2, 3, and 4 points in this study. This study assessed the flexors of elbow, wrist and fingers. MAS has also been shown to have excellent inter-rater reliability (ICC = 0.686-0.781) and intra-rater reliability (ICC = 0.644-0.748) in assessing spasticity in patients (Meseguer-Henarejos et al., 2018).

Modified Barthel Index (MBI): The MBI is a tool that is commonly used to assess the self-care ability of daily living, which reflects functional capacity, particularly in patients following stroke (Perez et al., 2018). In assessing patients following stroke, the MBI has shown excellent reliability (ICC = 0.88) (Yang et al., 2021).

### Data management

To protect participant confidentiality, all data collected will be assigned unique codes instead of using participants’ names. Data will be recorded on the case report form. The access of all data will be restricted to the principal investigator only. To ensure accuracy in data entry, the principal investigator will meticulously review the data entries for all participants. Monitoring of study conduct and data collection will be performed by a special committee of the University Clinical Trial Unit on a biannual basis. Following the guidelines set by the journal publication policy, the raw data collected during this research study will be securely stored for a period of up to five years after the publication of the initial paper.

### Statistical analysis

Before conducting parametric tests, several steps were taken to prepare and analyze the data. Outliers were identified using normal Q–Q plots and box plots, and data points that were more than three standard deviations from the mean were considered outliers and subsequently excluded from the analysis (Minati et al., 2011). Missing values were addressed using multiple imputation analysis to estimate and replace the missing data points (Blankers et al., 2010).

Descriptive statistics were used to summarize the demographic and clinical characteristics of the study participants. The normality of the data distribution was assessed using the one-sample Kolmogorov-Smirnov test. For comparisons between different groups, chi-square tests were used for categorical variables, while independent t-tests were used for continuous variables.

To evaluate the differences in outcome measures before and after the intervention for participants with stroke, paired sample *t*-tests were employed. The correlations between variables were assessed using either the Pearson correlation coefficient (r) or the Spearman correlation coefficient (ρ), depending on the nature of the data.

The significance of interregional coupling strength between the resting state and different grasping states was evaluated using a one-way analysis of variance (ANOVA). Additionally, χ^2^ tests were utilized to identify statistically significant differences in interregional coupling direction between the resting state and different grasping states.

All statistical analyses were performed using SPSS software (version 20.0; SPSS Inc., Chicago, IL, USA). All tests were two-tailed, and a significance level of *p* < 0.05 was considered statistically significant.

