### Participants

Inclusion Criteria:

1.First stroke confirmed by CT or MRI.2.Medically stable.3.Age between 40 and 80 years.4.Onset of stroke occurred between two weeks to three months.5.Right handedness.6.No severe cognitive impairment (MMSE ≥ 22 points) and able to follow motor commands.7.Able to maintain an upright position in an armless seat for at least 30 min.8.Modified Ashworth grade of the affected upper limb is equal to or less than grade 2.9.Brunnstrom motor function grade of the affected hand is equal to or greater than grade 3, and able to grasp a 2.5cm3 wood block with effort.10.Patient and their family members agree to participate in the study and have signed the informed consent.

Exclusion Criteria:

1.Unstable clinical condition.2.Presence of any neuropsychiatric illness other than stroke.3.Diagnosis of schizophrenia, bipolar disorder, obsessive-compulsive disorder, personality disorder, or major depression.4.Presence of skin lesions or infections on the upper limb.5.History of upper limb fractures, deformities, or finger absence.

Sample Size:

Based on the sample size of previous studies (Huo et al., 2019a), a total of 60 patients following stroke will be enrolled in this study, with 20 patients in each of the three groups.

Group A: Patients who can only grasp and lift a 2.5 cm^3^ wooden block with their hemiplegic hand.Group B: Patients who can grasp and lift 2.5 cm^3^ and 5 cm^3^ blocks with their hemiplegic hand but cannot lift 10 cm^3^ blocks.Group C: Patients who can pick up 2.5 cm^3^, 5 cm^3^, and 10 cm^3^ wood blocks with their hemiplegic hand but exhibit abnormalities in speed and coordination during the task.

In addition, a control group of 20 age-matched healthy subjects without neurological diseases or history of upper limb trauma will also be enrolled.

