### Limitations

There were several important limitations in this study that warrant consideration. Firstly, the trial sample size was relatively small. A small sample size can impact the statistical power of the study and may limit the ability to draw robust and generalizable conclusions from the findings. Secondly, the study design employed a non-randomized clinical trial approach, and participants were recruited using convenience sampling from the inpatient population with stroke. This could limit the generalizability of the findings. Thirdly, the study primarily focused on the assessment of hemodynamic changes during grasping motor tasks. Consequently, the understanding of the intervention’s effects on overall motor function may be limited by this narrow focus on specific upper limb tasks. Lastly, the two functional near infrared spectroscopy detection systems was at different sampling rate during the measurements.

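### The plan excludes every value beyond three SD on size alone, which can remove genuine extremes, understate standard errors and, for skewed outcomes or a pooled SD, bias means

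*Protocol article*

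**What the plan says.** All of the following is in the protocol article.

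- **Detection (Statistical analysis):** "Outliers were identified using normal Q–Q plots and box plots".
- **Exclusion (same sentence):** "data points that were more than three standard deviations from the mean were considered outliers and subsequently excluded from the analysis". This is placed before the parametric tests. It names no outcome to which it does not apply, and it asks for no evidence that the flagged value is an artefact or an entry error.
- **Missing data (next sentence):** "Missing values were addressed using multiple imputation analysis to estimate and replace the missing data points". The text does not say whether an excluded point then counts as missing.
- **Tests on the remaining data:** for group comparisons, "independent t-tests were used for continuous variables"; for before-and-after comparisons, "paired sample *t*-tests were employed".
- **Numbers (Participants):** "a total of 60 patients following stroke will be enrolled in this study, with 20 patients in each of the three groups", and "a control group of 20 age-matched healthy subjects without neurological diseases or history of upper limb trauma will also be enrolled".

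The section does not say whether the mean and SD in the rule are taken per group, per visit or over everyone.

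**The concern.** A size rule cannot tell a failed measurement from a patient who truly responds strongly. Two features of this trial make that matter.

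- **Extremes are part of the question.** The primary objective, at the end of the Introduction, includes the heterogeneity of muscle oxygenation. The Summary in the Discussion expects altered cortical activation and greater muscle oxygen consumption after stroke. Cutting tails reduces the spread that the trial sets out to describe.
- **Some technical problems are dealt with earlier.** Cortical preprocessing already removes artefacts (fNIRS system and data analysis of cerebral cortex), and all data entries are reviewed (Data management). A cortical or clinical value that is still extreme after these steps is more likely to be real.

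At stake is the validity of the t-tests and intervals. Deleting the largest deviations shrinks the SD, and the test then treats the trimmed sample as if it were the full one. For an asymmetric outcome the mean moves as well. In a paired comparison, deleting one visit also loses the pair unless the value is filled in.

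**Working it through.** The article gives no SD, skewness, effect size or power, so there is no figure of its own to reproduce. The check asks whether the rule can act at these sample sizes and what it then does under a range of assumed distributions.

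**1. Can the rule act?** With the sample's own mean and SD, the largest possible standardised deviation is (n−1)/√n.

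- n=20 (one group): 19/√20 = 4.25
- n=60 (all stroke patients): 59/√60 = 7.62
- n=80 (everyone): 79/√80 = 8.83

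All exceed 3, so the rule can delete values at each level.

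**2. Effect within one sample.** 40,000 simulated data sets per row. Points with |x − mean| > 3 SD were deleted once and not imputed. The mean, the SE (SD/√n of the remaining points) and the 95% t-interval were then computed.

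| Assumed data | n | Deleted per data set | Bias in mean | Change in SE | Coverage, all kept | Coverage, after deletion |
|---|---|---|---|---|---|---|
| Normal | 20 | 0.01 | none | −0.3% | 95.0% | 94.8% |
| Normal | 60 | 0.11 | none | −0.9% | 95.3% | 94.8% |
| t, 4 df | 20 | 0.15 | none | −8% | 95.3% | 94.5% |
| t, 4 df | 60 | 0.77 | none | −11% | 95.2% | 94.1% |
| Lognormal, log-SD 0.5 | 20 | 0.19 | −2.1% | −9% | 92.8% | 88.7% |
| Lognormal, log-SD 0.8 | 20 | 0.37 | −7.3% | −20% | 89.9% | 80.0% |
| Lognormal, log-SD 1.0 | 20 | 0.47 | −12.4% | −28% | 86.8% | 72.1% |
| Lognormal, log-SD 0.5 | 60 | 0.88 | −3.1% | −12% | 94.3% | 86.0% |
| Lognormal, log-SD 0.8 | 60 | 1.28 | −8.7% | −24% | 92.5% | 73.6% |
| Lognormal, log-SD 1.0 | 60 | 1.44 | −13.5% | −32% | 90.5% | 64.0% |

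In the symmetric rows deletions split about evenly between high and low values. In the lognormal rows essentially all are high.

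**3. Is the smaller SE actually too small?** Deletion also changes how much the mean varies, so the reported SE was compared with the true sampling SD of the mean.

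- Lognormal, n=20: the ratio falls from 0.96, 0.92 and 0.85 with all values to 0.87, 0.79 and 0.74 after deletion. The understatement is real and large.
- t with 4 df: from 0.954 to 0.947 at n=20, and from 0.984 to 0.953 at n=60. Most of the SE reduction reflects a less variable mean. The type I error of the test on paired differences rises from 4.8% to 5.6% at n=20 and from 4.7% to 6.0% at n=60, so the harm is modest.

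**4. If the mean and SD were pooled over all 80.** One group of 20 is shifted from three normal groups with SD 1.

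| Shifted group | Deletions per data set | Share from that group | Its mean after deletion |
|---|---|---|---|
| Shift 1, SD 1 | 0.16 | 57% | 0.99 |
| Shift 2, SD 1 | 0.11 | 90% | 1.98 |
| Shift 1.5, SD 1.5 | 0.51 | 98% | 1.41 |
| Shift 1, SD 2 | 0.88 | 99.6% | 0.86 |

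With within-group limits the same group loses about 0.01 values per data set in every row.

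**The case against.** **The effect may be negligible.** With roughly normal data and within-group limits it is: about one deletion per hundred groups of 20. Wavelet amplitude is averaged over the channels of a region, which tends to reduce skew, and nothing in the article supports a log-SD as high as 0.8 or 1.0. This stands. The upper rows of the range are illustrations and not estimates for this trial.

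**Group contrasts are partly protected.** If two groups are equally skewed, both means fall by about the same proportion and their ratio hardly changes. This stands for the ratio. The standard error still suffers: for two lognormal groups of 20 with no difference, the type I error of the t-test rises from about 4–5% to 7% or more.

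**Safeguards and details may lie elsewhere.** The article describes artefact removal and plots, and the level at which the SD is taken, transformations and sensitivity analyses may be in a fuller document. Their absence is not the point here. The point is the rule that the article does state, which excludes on size. The artefact step is described for the cortical signal only, so an extreme muscle value might be a technical failure. That calls for a technical check, which a size rule does not supply.

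**Three stronger readings are tempting, and the text does not support them.**

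- *Deleted values are then imputed.* Exclusion and imputation stand in adjacent sentences, but nothing links them. Read plainly, missing values are those not collected.
- *Mostly high values are lost.* This needs right skew, which is plausible for wavelet amplitude but shown nowhere. Activation betas, the lateralization index and haemoglobin concentration changes are signed, and the clinical scales are bounded and could lose low values instead.
- *The most abnormal group loses most.* This needs limits pooled across groups, which the article does not state.

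**Conclusion.** The concern holds in a limited form. The article fixes an exclusion rule based on size alone, for all outcomes, and that rule can discard genuine responses. The damage depends on the data:

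- **Normal, within-group limits:** negligible.
- **Symmetric and heavy-tailed:** means unbiased, slight anti-conservatism (type I error 5.6–6.0% instead of 4.7–4.8%).
- **Right-skewed:** means too low, standard errors clearly too small, and interval coverage well below nominal. Deletion costs about 4, 10 and 15 percentage points at n=20 for log-SD 0.5, 0.8 and 1.0 (92.8−88.7, 89.9−80.0, 86.8−72.1). Coverage after deletion is lower still at n=60.
- **Limits pooled across groups:** deletions concentrate in a group that is shifted or more variable, and its mean is pulled towards the others.

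All sizes rest on assumed distributions, because the article gives none. Fewer than half a value per group of 20 is deleted in the within-group cases, so a reader should not conclude that the rule erases the abnormality under study. It trims the tails and makes the remaining data look more precise than they are. The rule should be changed, since doing so costs little.

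**What to change.** Replace the 3-SD exclusion in the Statistical analysis section with the following:

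1. Exclude a channel, block or value only for a documented technical cause, such as saturation, poor optode coupling, motion or a confirmed entry error, judged blind to group and visit.
2. Keep every other measured value in the main analysis. For skewed measures use a log transformation, or robust or rank methods.
3. Report the 3-SD exclusion only as a sensitivity analysis, stating the level at which the mean and SD are taken and the number of values removed by group and visit.
4. Since the text leaves it open, state that a measured value that was excluded is not treated as missing and imputed. Such a value would be absent because of its own size, which breaks the missing-at-random assumption on which standard multiple imputation rests.

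The cost is a change of wording and somewhat wider intervals for skewed measures. That extra width is uncertainty that the deletion rule would hide. No added data collection is needed beyond recording the technical reasons.
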